### 9-2. Examination Items

#### 1) Background of Participants

- The following items will be investigated:
- Gender, date of birth, smoking and drinking status
- Presence of chronic diseases
- Use of medication
- Use of supplements
- Intake of polyphenols
- Presence of allergic conditions
- Pregnancy status
- Height and weight
- Changes in lifestyle habits during the study period (such as changes in exercise habits and workplace)

#### 2) Measurement of Height and Weight

Participants will have their height and weight measured after arriving at the testing site.

#### 3) Resting Measurements (Respiratory Gas Analysis and Thermography Camera

#### Imaging)

Measurements will be conducted in a laboratory set at  $27 \pm 1^{\circ}\text{C}$ . Participants will wear light clothing consisting of a tank top with an open neckline and shorts, and will remain at rest for 30 minutes. After resting, baseline skin temperatures of the supraclavicular area and fingertips will be recorded using a thermography camera. Following this, respiratory gas analysis will be performed.

#### 4) Dietary Intake

After the resting measurements, participants will consume a specified meal. The meal will be provided to account for 15% of the total energy expenditure based on the Harris-Benedict Calculator, and participants will consume it with 200 mL of water.

#### 5) Postprandial Measurements

Measurements will be taken 30, 60, 90, 120, 150, and 180 minutes after the start of the meal, including thermography camera imaging of the supraclavicular area and fingertips, as well as respiratory gas analysis.

#### 6) Visual Analog Scale (VAS) Assessment

Participants will be handed a VAS assessment form before the meal starts and again after the 180-minute postprandial measurement to record their subjective indicators.

#### 7) Dietary Record

After the trial begins, participants will be required to maintain a dietary record diary.

### **9-3. Random Allocation**

An allocation officer will be designated separately from the trial personnel (study director, trial implementers, and data analysts) to manage the order of treatment allocation for the participants. Participants will be allocated based on stratified randomization considering factors that may influence brown adipose tissue function, such as age, BMI, and gender. Allocation will be performed using a random number table, and the allocation information will not be disclosed to the trial implementers and participants during the study (ensuring double blinding). The allocation information will be revealed to the trial implementers by the allocation officer after all measurements for the participants have been completed and after a predetermined period.

## **10. Outcomes**

### **10-1. Primary outcome**

Changes in postprandial thermogenesis and energy expenditure after four weeks of intake.

### **10-2. Secondary outcomes**

- 2) Changes in body composition after four weeks of intake.
- 3) Changes in oxygen consumption, carbohydrate oxidation, fat oxidation, and respiratory quotient after four weeks of intake.
- 4) Changes in subjective indicators after four weeks of intake.

## **11. Termination and Dropout from the Study**

### **11-1. Criteria for Study Termination**

The study will be terminated if any of the following events occur after registration. When terminating the study, observations, tests, and evaluations will be conducted as promptly as possible.

- 1) If an adverse event occurs that leads the principal investigator to determine that continuing the study is not feasible.
- 2) If a participant requests to withdraw from the study.
- 3) If, for any other reason, the principal investigator determines that continuing the study is not feasible.

### **11-2. Study Dropout**

Participants will withdraw from the study and no further investigations will be conducted if any of the following occur after registration:

- 1) The participant cannot continue the study due to personal circumstances (such as relocation) or other reasons.
- 2) The participant requests to terminate their participation in the study or withdraws consent. In such cases, the participant's intent to withdraw from the study will be obtained using the "Consent Withdrawal Form" (Appendix).

## **12. Response to Adverse Events**

### **12-1. Adverse Events**

An adverse event refers to any undesirable or unintended health problem or symptom experienced by a participant, regardless of its causal relationship with the research. In the event of an adverse event, the responsible physician will take prompt and appropriate action to ensure the participant's safety. Additionally, if treatment for the adverse event is necessary, the participant will be informed accordingly.

## **12-2. Reporting of Adverse Events**

In the event of a serious adverse event, the responsible physician will promptly report it in writing to the head of the research institution. Additionally, communication for reporting in accordance with the safety information reporting system for pharmaceuticals and medical devices, as stipulated in the “Law on Securing Quality, Efficacy, and Safety of Pharmaceuticals and Medical Devices,” will be carried out appropriately in accordance with the regulations of each research facility.

## **13. Data Collection**

13-1. The investigator will appropriately record and store the investigation items.

13-2. Data Management

Data modification and database management will be conducted, with the creation of statistical analysis datasets performed at Juntendo University.

## **14. Statistical Analysis**

Measurements and changes will be compared using appropriate statistical analysis methods such as paired t-tests, analysis of variance (ANOVA), and multiple comparison tests.

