## **8. Research Methods**

### **8-1. Study Design**

Multicenter, randomized, crossover, double-blind.

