### **8-2. Outline of the Study**

The researcher will obtain consent from the participants and confirm their eligibility before commencing the trial. The duration of participants' involvement in the study will be as follows:

1. Eligibility assessment and consent form acquisition.
2. Consumption of the test food for four weeks, with testing conducted in the fourth week of consumption.
3. Washout period of four weeks.
4. Change of test food, followed by the consumption of the new test food for four weeks, with testing conducted in the fourth week of consumption.
5. Study conclusion.

A schematic outline is provided below.

[figure not shown]

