### 8-3. Target Sample Size and Study Period

Target sample size: 36 participants (6 participants from Juntendo University, 30 participants from Niigata University)

Maximum enrollment period: From the date of approval to March 31, 2024

Study period: From the date of approval to March 31, 2024

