## **15. Target Sample Size and Rationale**

36 participants.

[Rationale for Setting Criteria]

In a preliminary open-label, before-and-after comparison study involving 10 participants, the effects of the test food on brown adipose tissue were evaluated. The increase in skin temperature in the supraclavicular area during cold exposure before and after the consumption of the test food was used as an indicator to analyze the function of brown adipose tissue. Based on this data, the sample size was calculated with a power of 95%

and a significance level of 0.05, resulting in a calculated sample size of 22 participants. However, since this study uses different indicators than the preliminary trial, previous literature was referenced, and significant differences were observed in a crossover trial involving 36 participants. Therefore, it was assumed that a sample size of more than 22 and less than 36 participants would be necessary to obtain significant differences in this study, leading to the establishment of the sample size of 36.

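### Section 14 lists paired t-tests first for a two-period crossover and names no period or sequence term; the primary comparison should be a crossover model

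*Protocol*

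**What the plan says.** Protocol section 8-1 describes the design as "Multicenter, randomized, crossover, double-blind". Section 8-2 sets four weeks on one drink with testing in the fourth week, then "Washout period of four weeks", then "Change of test food, followed by the consumption of the new test food for four weeks, with testing conducted in the fourth week of consumption". The two tests therefore fall near weeks 4 and 12, about eight weeks apart. The outline describes no test before intake in either period.

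On allocation, section 9-3 says "Participants will be allocated based on stratified randomization considering factors that may influence brown adipose tissue function, such as age, BMI, and gender" and "Allocation will be performed using a random number table". It gives no block size and does not state an equal split between the two orders.

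Section 14 is a single sentence. Measurements and changes will be "compared using appropriate statistical analysis methods such as paired t-tests, analysis of variance (ANOVA), and multiple comparison tests". It does not say which of these serves the primary outcome or what terms the ANOVA would contain. The protocol mentions no period, sequence or carryover term.

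**The concern.** In a two-period crossover, anything that shifts the measurement between the first and second test day enters each juice-minus-placebo difference. It enters with one sign in participants who take juice first and the opposite sign in those who take it second. A paired t-test pools these differences as if they came from one distribution. With equal sequences the shift cancels in the mean but inflates the standard deviation, so power is lost. With unequal sequences it does not fully cancel, and the estimate is biased.

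A shift of this kind is credible. The test days are two months apart, and each session involves rest, a test meal and repeated gas analysis over 180 minutes, which may feel different the second time (an inference, not a statement in the protocol). The protocol itself expects exercise habits and diet to influence the outcomes (section 6-4, rationale). As described, no pre-period measurement is available to absorb the shift. Unequal sequences are also possible, because no equal split is stated and section 11-2 allows withdrawal after registration.

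**Working it through.** **The plan's own figure.** Section 15 reports 95% power "and a significance level of 0.05, resulting in a calculated sample size of 22 participants", and the trial then sets 36. The 22 cannot be reproduced forward, because neither the pilot's mean change nor its SD is given. Solved backwards for a paired test, 22 at 95% power implies a standardised difference of 0.807 (two-sided 0.05) or 0.725 (one-sided). That calculation concerns another endpoint, so it gives no effect size for this comparison.

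**Inputs.**
- N = 36: section 8-3.
- Two-sided 5% level: section 15 gives 0.05; two-sided is assumed.
- Treatment effect τ: assumed. A paired test with N = 36 and no period effect has 80% power at 0.480 SD and 90% power at 0.556 SD.
- Period effect π (period 2 minus period 1): assumed, 0 to 0.75. The unit is the SD of the within-person treatment difference.
- Sequence split n1:n2: assumed, from 18:18 to 24:12.

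**Model.** The within-person difference is D = τ + π if juice comes second (n1 people) and D = τ − π if it comes first (n2 people), plus error with SD 1.

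**Balanced sequences.** The mean of D is τ, so there is no bias. The SD seen by the paired test is about √(1 + π²). At π = 0.5 that is √1.25 = 1.118. Simulated power at 18:18:

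| π (SD) | Paired t, τ = 0.480 | Paired t, τ = 0.556 | Paired t, type I error |
|---|---|---|---|
| 0 | 80% | 90.0% | 5.0% |
| 0.25 | about 78% | 88.8% | 4.3% |
| 0.5 | about 72% | 85.1% | 2.9% |
| 0.75 | about 63% | 78.1% | 1.5% |

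The period-adjusted analysis stays at 80% and 90% throughout, with type I error of about 5%.

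**Unequal sequences.** The bias of the paired estimate is π × (n1 − n2)/N. At π = 0.5:

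| Split | Bias (SD) | Paired t, type I error |
|---|---|---|
| 20:16 | 0.5 × 4/36 = 0.056 | 3.7% |
| 21:15 | 0.5 × 6/36 = 0.083 | 5.0% |
| 24:12 | 0.5 × 12/36 = 0.167 | 11.9% |

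At 21:15 the bias is half the nominal standard error (1/√36 = 0.167) and 17% of the assumed 0.480 SD effect (0.083/0.480). The adjusted estimate is unbiased at every split.

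**How likely is imbalance?** Under simple 1:1 randomisation of 36, a difference of at least 6 between sequences has probability 41%, and of at least 12, 6.5%. Blocking within strata would lower both figures; the protocol does not say whether blocks are used.

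**Price of adjusting when π = 0.** The variance of the adjusted estimate is (1/4)(1/n1 + 1/n2), against 1/N for the paired mean. The ratio is 1.000 at 18:18, 1.029 at 21:15 and 1.125 at 24:12. Degrees of freedom fall from 35 to 34. Simulated power at τ = 0.556 is 90.0% for both methods at 18:18, 90.0% against 89.2% at 21:15, and 90.1% against 86.3% at 24:12.

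**The case against.** The strongest objection is that section 14 commits to nothing. It gives examples, ANOVA stands in the same sentence, and a crossover ANOVA can carry period and sequence. Model terms are often left to a statistical analysis plan, which may exist and is not shown. This stands in part. A reader might infer that the protocol has chosen the paired t-test for the primary outcome, and the text does not support that. But section 14 does name a test with no period term, places it first, and gives the ANOVA no terms. An analyst could run the paired t-test and comply fully.

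The second objection is that nothing shows a period effect exists. This also stands. The conditions are standardised: a room at 27 ± 1 °C, light clothing and 30 minutes' rest (section 9-2); a specified dinner and fasting after 21:00 (section 8-4); and exclusion of people expecting lifestyle changes (section 6-4). A reader might take the Background to say that thermogenesis varies by season. It speaks of cold environments and does not mention season. At 0.25 SD the balanced power loss is only one to two points.

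Third, the bias depends on the imbalance that happens to arise and averages to zero over repeated 1:1 randomisation. A reader might also infer a general inflation of false positives. The figures do not show one: the paired test is conservative at 18:18 and near 5% at 21:15 with a 0.5 SD shift. In the 0.5 SD calculations only 24:12 exceeds 5%.

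**Conclusion.** The point holds conditionally, as a cheap improvement. The protocol permits a paired t-test for the primary juice-placebo comparison and specifies no analysis that uses period or sequence. If that test is used and a period effect exists, balanced sequences cost about 2, 8 and 17 points of power at 0.25, 0.5 and 0.75 SD, starting from 80%. Unequal sequences bias the estimate by the period effect times (n1 − n2)/N, given the realised split.

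These sizes rest on assumptions that the documents neither confirm nor exclude: the period effect, the sequence split and the treatment effect. The 0.480 SD is simply what 36 participants detect with 80% power and is not an effect the trial planned for. If there is no period effect, nothing is lost by the paired test. The case for the change is that protection costs almost nothing at plausible splits, while the possible loss is material from about 0.5 SD upwards.

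**What to change.** In section 14, name the primary analysis: a linear mixed model on the values from the two test days, with treatment, period and sequence as fixed effects and participant as a random effect. With complete data its treatment estimate and test match the two-sample comparison of within-person period differences between the two sequences. Keep the paired t-test as a sensitivity analysis. If a statistical analysis plan already specifies such a model, the edit only brings the protocol into line with it.

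The change needs no new data and can be made in one sentence. It costs one degree of freedom, and if there is no period effect at most about one percentage point of power at splits from 18:18 to 21:15. At a split as uneven as 24:12 the cost would be about four points (90.1% to 86.3%), but that is also where the paired test is most exposed to bias.

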## **15. Target Sample Size and Rationale**

36 participants.

[Rationale for Setting Criteria]

In a preliminary open-label, before-and-after comparison study involving 10 participants, the effects of the test food on brown adipose tissue were evaluated. The increase in skin temperature in the supraclavicular area during cold exposure before and after the consumption of the test food was used as an indicator to analyze the function of brown adipose tissue. Based on this data, the sample size was calculated with a power of 95%

and a significance level of 0.05, resulting in a calculated sample size of 22 participants. However, since this study uses different indicators than the preliminary trial, previous literature was referenced, and significant differences were observed in a crossover trial involving 36 participants. Therefore, it was assumed that a sample size of more than 22 and less than 36 participants would be necessary to obtain significant differences in this study, leading to the establishment of the sample size of 36.

## **16. Ethics**

This study will be conducted in accordance with the principles of the latest Declaration of Helsinki to protect the rights and welfare of patients, and in compliance with the guidelines of the "Ethical Guidelines for Medical Research Involving Human Subjects" issued by the Ministry of Education, Culture, Sports, Science and Technology and the Ministry of Health, Labour and Welfare.

### **16-1. Ethical Review**

The responsible physician will seek the opinions of the ethics review committee of the research representative's affiliated institution and obtain permission from the head of the research institution prior to conducting the study.

### **16-2. Protection of Personal Information**

Individuals involved in the conduct of this study will take appropriate measures to ensure the privacy and protection of participants' personal information. The registered participant information will be anonymized by assigning a registration number specifically for this study. Reports will not include any identifiable information such as names or numbers. When publishing the results of the study, no information that could identify participants will be included. Data obtained from participants during the study will not be used for purposes other than those of this research; if there is a need to use it for purposes other than research, separate consent will be obtained from the participants as necessary.

### **16-3. Compensation for Health Damages**

If any health damages occur to participants as a result of this study, the research facility will take necessary measures, including treatment. The costs of treatment will be covered by the health insurance of the participants.

### **16-4. Benefits and Risks for Participants**

The results of this study may establish a method to improve the efficiency of postprandial

thermogenesis and energy expenditure through the intake of food components, thus improving the balance of energy intake and expenditure. Improving this balance is important for the prevention of various diseases associated with obesity and aging, and it is expected to contribute to the advancement of medicine in the future. The test foods used in this study are within the range of what is typically consumed in a normal diet, and it is believed that the risk of experiencing any disadvantages is extremely low.

#### **16-5. Financial Burden on Participants**

The costs associated with the trials conducted on research participants will be funded by the collaborative research funds from Juntendo University, Niigata University, and Bourbon Corporation. Participants who cooperate through to the end will receive a compensation fee (7,000 yen per day for measurements over 2 days plus a burden fee of 6,000 yen for food intake, totaling a 20,000 yen voucher). Payments will be appropriately managed through receipts and payment records.

### **17. Quality Control and Quality Assurance**

#### **17-1. Data Handling**

Trial data will be stored at Juntendo University for ten years from the date of the report on the discontinuation or completion of the study.

#### **17-2. Record Keeping**

Documents related to the study, such as consent forms, participant number correspondence tables, examination data, and approval letters from the ethics review committee, will be stored at the research implementing facility and will be discarded ten years after the study is discontinued or completed.

#### **17-3. Monitoring and Auditing**

Regarding Monitoring Implementation

Self-monitoring will be conducted at the start, during any changes, at the end, and at least once a year.

Self-Monitor: [name]

Regarding Auditing Implementation

No auditing will be conducted. Monitoring will be carried out in accordance with the

"Procedures for the Implementation of Monitoring and Auditing in Medical Research Involving Human Subjects" (Clinical Research Support Center).

#### **17-4. Reporting to the Head of the Research Institution**

Researchers will promptly report to the head of the research institution if significant concerns arise regarding the leakage of information related to the research, ethical considerations for the rights of research participants, or issues concerning the conduct of the research.

Researchers will promptly report to the head of the research institution if they obtain information that may compromise the appropriateness of the research implementation or the trustworthiness of the research results.

The principal investigator will report to the head of the research institution without delay if they obtain any facts or information that may undermine the ethical validity or scientific rationality of the research, which may impact the continuation of the study (except in cases referred to in point 4).

The principal investigator will report the progress of the research and the occurrence of adverse events associated with the study to the head of the research institution as stipulated in the research protocol.

The principal investigator will report necessary matters to the head of the research institution when the research is concluded (including in cases of termination).

### **18. Research Funding and Conflict of Interest**

#### **18.1. Research Funding**

This study will be conducted using the collaborative research funds from Juntendo University, Niigata University, and Bourbon Corporation, with funding provided by Bourbon Corporation. Additionally, individuals affiliated with the collaborative research course at Juntendo University, funded by Bourbon, are involved in this study.

#### **18.2. Conflict of Interest**

The principal investigator and co-investigators include members affiliated with Bourbon Corporation, the funding provider, as well as individuals in the collaborative research course at Juntendo University funded by Bourbon. However, measurements will be carried out by investigators from Niigata University who do not have a direct conflict of interest with Bourbon to ensure that Bourbon does not have any involvement in these

aspects. Furthermore, blinding will be maintained until all data analyses are completed to prevent any potential bias that could favor Bourbon Corporation. All researchers will manage conflicts of interest appropriately in accordance with their respective organizations' conflict of interest management policies and will disclose such conflicts upon request when presenting research results at conferences or publishing in medical journals.

